**7 Outcome measures**

**7.1 Fugl-Meyer motor assessment- upper extremity**

The Fugl-Meyer motor assessment- upper extremity (FMA-UE) is the main index used in this study to measure upper limb motor dysfunction after stroke. It is a cost-effective clinical examination method that is widely used in stroke patients due to its reasonable design, simplicity, and ease of use^[45]^. The FMA-UE assesses reflex activities, shoulder, elbow, and wrist joint movement, as well as coordination. It consists of 8 aspects and 33 items, with each item scored on a scale of 0 to 2 points. The total score ranges from 0 to 66 points.

**7.2 Wolf Motor Function Test**

The Wolf Motor Function Test (WMFT) is a rehabilitation scale used to assess the motor function of the upper limbs in individuals who have had a stroke^[46]^. Unlike the FMA, which primarily assesses the coordination function of stroke patients, the WMFT can evaluate both impairment and the impact of training on disability^[47]^. Additionally, it can reflect the effects of various functional task trainings on patients. The test consists of 15 items, with the first six focusing on simple joint movements and the remaining nine involving compound functional movements. Each action is timed and scored based on the quality of the movement using a six-grade scale ranging from 0 to 5 points.

**7.3 Absolute angular error**

Absolute angular error (AAE) is defined as the absolute difference between the target angle and the patient's perceived elbow flexion angle. It is used to assess the patient's proprioception and motor control^[36]^. In this study, we set the target angle to 90° of elbow flexion and an angular velocity of 2°/s, as measured by the upper limb intelligent feedback training system for evaluating upper limb proprioception. During the training session, the patient wears eye masks and earmuffs to minimize any external influence on proprioception. The patient is instructed to move the affected upper limb from the vertical position to the target position, memorize the target position, take a 10-second rest, and then repeat the same movement. The difference between the target position and the measured position is recorded as the absolute error angle. A smaller absolute error angle indicates a better position sense.

**7.4 Joint Movement Angle**

Joint Movement Angle (JMA) is a method that utilizes a goniometer to measure the maximum angle of active movement in the joints of the upper limb. The measured upper limb joint movements include shoulder flexion, shoulder extension, shoulder abduction, shoulder adduction, shoulder external rotation, shoulder internal rotation, elbow flexion, forearm pronation, and forearm supination. It is important to note that a larger angle of active movement indicates better motor function.

**7.5 Modified Barthel Index**

The improvement in basic activities of daily living can be assessed using the Modified Barthel Index (MBI), a commonly used tool for evaluating the ability of stroke patients to perform daily tasks. The MBI consists of 10 tasks, which are scored based on the time and assistance required by the patient to complete them. These tasks include eating, bathing, dressing, washing and grooming, control of defecation, control of urination, using the toilet, going up and down stairs, transferring from bed to chair, and walking 45 meters on level ground. Transferring from bed to chair and walking 45 meters on level ground have the highest scores of 15 points, while grooming and bathing have a maximum score of 5 points. The other six tasks have a maximum score of 10 points each. The lowest score for each task is 0 points, and the total score ranges from 0 to 100. A lower score indicates a greater dependence on care, while a score of 60 or higher suggests the ability to take care of oneself.

**7.6 Stroke-specific quality of life**

Stroke-specific quality of life (SS-QOL) is a patient-reported prognostic indicator used to assess the health-related quality of life in stroke patients. It can also be reported as a secondary outcome. The content of SS-QOL includes 49 items distributed across 12 domains, such as energy, family roles, language, mobility, mood, personality, self-care, social roles, thinking, upper body function, vision, and work/productivity. Each domain is scored separately, with a maximum score of 5 points for each item. The scores are then calculated to obtain the total score. A higher score indicates better functioning.

**8 Statistical method**

The clinical data will follow the per-protocol (PP) analysis and intention-to-treat (ITT) analysis. PP analysis was applied to all the randomized participants who will not stop treatment prematurely, and complete 4 weeks of treatment. ITT analysis is applied for participants who have dropped out of the trial, according to the rule of last-observation-carried-forward. The normality test of the measurement data is performed using the Shapiro-Wilk method, and the conformity distribution is expressed as the mean ± standard deviation. P<0.05 is significant for the difference. Categorical data, such as gender or those expressed as frequencies (%) will be analyzed using the chi-square test or Fisher’s exact test. Perform nonparametric statistical tests on data that do not conform to the normal distribution. In addition, statistically significant differences in intra-group and inter-group data will be analyzed by repeated measurements of ANOVA. All statistical analysis will be performed using IBM SPSS version 25.0 (SPSS Inc., Chicago, IL, USA). Missing data patterns will be analyzed by missing value analysis.

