**2 Eligibility criteria**

**2.1 Inclusion criteria**

1. Presence of stroke documented by CT or MRI, including ischemic and hemorrhagic stroke;
2. Subacute stage of stroke (first onset, duration of disease within 6 months);
3. Ability to sit and balance without upper limb support, and able to tolerate at least half an hour of training or testing;
4. Brunnstrom classification of the patient's upper limb is ≤4;
5. Stable blood pressure (less than 160/100 mmHg);
6. Good cognitive ability (Mini-Mental State Examinatione score ≥22)^[43]^;
7. Good muscle tone (modified Ashworth classification < level 2);
8. No severe visual impairment or visual field defect;
9. Age between 35-80 years old, with no gender limit.

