**2.3 Elimination and discontinuation criteria**

1. Patients who provided incomplete information, leading to missing data on the main outcome indicators;
2. Patients who provided false information;
3. Patients with other systemic diseases that made them unsuitable to continue participating in the study;
4. Patients who experienced sudden illness or adverse events during the trial intervention period and were unable to continue or participate in the training;
5. Participants who voluntarily withdrew from the study;
6. Participants who experienced adverse events.

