**4 Randomized grouping and allocation concealment**

In this study, a total of 93 subjects will be evenly divided into 3 groups, with 31 cases in each group. The groups will be named as follows: BWS-TCY group, CRT group, and RAT group. Subject randomization will be performed by an external professional statistician. After baseline testing, each participant received an envelope containing a randomly assigned serial number to determine their group. The random sequence will be generated by an independent professional statistician using SPSS software (IBM Corp., IBM SPSS Statistics, V25, Armonk, NY, USA), with the random number seed set to 20210608. Throughout this process, the statisticians, outcome assessors, and data analysts will be blinded to the study's recruitment, intervention, and evaluation. The randomization assignments ill be placed in sealed opaque envelopes by an independent researcher who will be also blinded to the trial. The identity of each participant is represented by a serial number, which is numbered according to their entry into the group. The letters 'A', 'B', and 'C' are used to represent the assigned groups, with 'A' corresponding to the BWS-TCY group, 'B' to the CRT group, and 'C' to the RAT group. The randomization process will be conducted by an independent researcher. Three rehabilitation therapists will be responsible for recruiting and assigning participants to conduct the intervention. Due to significant differences between the groups, neither the researchers nor the therapists will be blinded. The study will be designated as open-label, so the patients will be not blinded.

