**6 Interventions**

All patients will receive rehabilitation intervention in addition to routine medical treatment and daily care in the hospital. The patient's safety status will be continuously recorded throughout the intervention. The rehabilitation intervention will last for 12 weeks, with sessions of 60 minutes per day, 5 days per week.

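### Section 8 misstates intention-to-treat as an analysis of dropouts completed by LOCF, and no set of all randomised patients analysed as allocated is defined

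*Protocol*

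**What the plan says.** Section 8 (Statistical method) opens with two analysis sets: "The clinical data will follow the per-protocol (PP) analysis and intention-to-treat (ITT) analysis". It then describes each.

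- Per-protocol: "PP analysis was applied to all the randomized participants who will not stop treatment prematurely, and complete 4 weeks of treatment".
- Intention-to-treat: "ITT analysis is applied for participants who have dropped out of the trial, according to the rule of last-observation-carried-forward".

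LOCF is the only rule given for filling in missing values. The section also plans an analysis of missing-data patterns, but that describes the gaps and is not an alternative way of estimating the treatment effect.

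Section 2.3 (Elimination and discontinuation criteria) includes "Patients who provided incomplete information, leading to missing data on the main outcome indicators" and "Participants who experienced adverse events", as well as voluntary withdrawal. It does not say which of these end treatment only and which also remove a patient from the analysis.

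Three other statements bear on the point. The population is defined by "Subacute stage of stroke (first onset, duration of disease within 6 months". Section 4 says "The study will be designated as open-label, so the patients will be not blinded". The Project summary and Study design describe assessment before and after the intervention and mention no visit in between.

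**The concern.** An intention-to-treat set keeps the comparison that randomisation created: everyone randomised, in the arm to which they were assigned. Section 8 ties ITT to the dropouts and gives the completers to PP. Read as written, neither set is the full randomised population. PP selects on completing treatment, and the ITT set selects on not completing it. A later SAP could repair this only by contradicting the sentence.

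LOCF is a separate fault and remains whatever ITT was meant to be. Patients are within 6 months of a first stroke and every arm receives active rehabilitation, so FMA-UE is expected to rise. With only a before and an after assessment, a patient who leaves without the second one has only a baseline score. LOCF enters that score as the final result, which amounts to assuming no recovery. The filled-in value then counts as a real observation, so the standard errors ignore the uncertainty of the imputation. Because patients and therapists know the allocation, dropout may differ between arms.

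At stake are the population and the estimator behind the primary FMA-UE comparison.

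**Working it through.** **Inputs from the protocol**

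- Section 3: 84 patients before dropout, 10% dropout, 93 in total, 31 per arm.
- Section 3, pilot of 15 patients split 1:1:1 (5 per arm), FMA-UE at 4 weeks: 35.5 ± 9.5 (BWS-TCY), 34.28 ± 9.58 (RAT), 29.00 ± 10.2 (CRT).
- Pilot differences: 35.5 − 34.28 = 1.22 versus RAT; 35.5 − 29.00 = 6.5 versus CRT.

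**Assumptions, because the protocol gives no figure:** baseline FMA-UE (15 to 25, equal across arms), dropout by arm, dropouts with a baseline score only, and dropouts who would otherwise have reached their arm's mean.

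**1. The plan's own total.** 84 × 1.10 = 92.4, which rounds up to 93. Dividing by 0.9 gives 93.3, or 94 if rounded up. The stated 93 is reproduced within rounding, and nothing below depends on the difference.

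**2. Size of the sets as worded.** At 10% dropout, 0.10 × 93 = 9.3. The ITT set would hold about 9 patients, about 3 per arm, and the PP set about 84. A correctly defined ITT set holds 93.

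**3. LOCF with equal dropout.** Expected arm mean = (1 − d) × final + d × baseline. With the same d and the same baseline in both arms, baseline cancels and the difference becomes (1 − d) × true difference.

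- Versus CRT: 0.9 × 6.5 = 5.85.
- Versus RAT: 0.9 × 1.22 = 1.10.

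This is dilution only.

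**4. LOCF with unequal dropout, simple form.** If both arms would gain G and dropout differs by p, the contrast shifts by p × G against the arm that loses more patients. With p = 0.10:

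- G = 5: 0.5 points
- G = 10: 1.0 point
- G = 15: 1.5 points

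Set against the pilot, 0.5 to 1.5 points is 0.5/6.5 = 8% to 1.5/6.5 = 23% of the CRT contrast, and 0.5/1.22 = 41% to 1.5/1.22 = 123% of the RAT contrast.

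**5. The same with the pilot means.** Worked case with 5% dropout on BWS-TCY, 15% on RAT and baseline 20:

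- BWS-TCY: 0.95 × 35.5 + 0.05 × 20 = 34.725
- RAT: 0.85 × 34.28 + 0.15 × 20 = 32.138
- Difference: 2.59, where the true value is 1.22

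Range over baseline 15 to 25:

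| Dropout, BWS-TCY / comparator | Versus RAT (true 1.22) | Versus CRT (true 6.5) |
|---|---|---|
| 10% / 10% | 1.10 | 5.85 |
| 5% / 15% | 3.09 to 2.09 | 7.58 to 6.58 |
| 15% / 5% | −0.89 to 0.11 | 4.12 to 5.12 |

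With no true difference (both arms reaching 29), the gain is 14 to 4 points. The 10-point dropout gap alone then creates 1.4 to 0.4 points.

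**6. Section 2.3 against section 8.** LOCF can keep a dropout in the analysis only if that patient has not been eliminated. If the section 2.3 list governs the analysis sets, the patients whom LOCF is meant to rescue have already been removed. The two sections cannot both be applied to the same patients.

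**7. Duration.** The PP criterion is 4 weeks of treatment, and Study design also gives 4 weeks. Section 6 says "The rehabilitation intervention will last for 12 weeks, with sessions of 60 minutes per day, 5 days per week", and the Project summary, section 6.3 and Duration of the project also give 12 weeks. The PP set cannot be determined until these agree.

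**The case against.** The strongest reply is that the sentence is loosely worded. An analysis of about 9 dropouts would serve no purpose, LOCF makes sense chiefly as a way of keeping dropouts in the full set, and the protocol's English is uneven throughout. That reading is plausible. However, the protocol does not say it, section 2.3 points the other way, and the LOCF objection is untouched by it.

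Three stronger readings are tempting and not supported:

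- A reader might infer that patients would be compared outside their randomised groups. Nothing says so. The fault is in who is included, not in the arm to which they are assigned.
- A reader might infer that, with PP and ITT listed unranked, a favourable PP result would be presented as the answer. The ranking can be left to a SAP that is not shown, and the rest is conjecture about conduct.
- A reader might infer a bias of known size and direction. The shift rests on an assumed gain, an assumed dropout gap and carry-forward from baseline, and under equal dropout it is dilution only. If there were interim assessments, less of the gain would be missed. The 1.22 benchmark is itself weak: with 5 patients per arm its standard error is √(9.5²/5 + 9.58²/5) = 6.0 points.

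A further fair point concerns the remedy. With one post-baseline assessment, a mixed model that uses baseline FMA-UE as a covariate drops every patient who has only a baseline score. It would be a completers' analysis under another name.

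**Conclusion.** The point holds in a limited form. ITT is misstated in section 8, no set of all randomised patients as allocated is defined anywhere in the protocol, and the elimination list in section 2.3 conflicts with such a set. These are faults in what the text states, not matters merely left to a SAP.

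LOCF is unsuitable for patients expected to recover, on either reading of ITT. The direction of its error depends on the dropout pattern. The range of 0.5 to 1.5 points is illustrative: modest against the CRT contrast and similar in size to the RAT contrast. The need for correction rests on the faulty definition and the imputation rule, not on those figures.

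**What to change.** 1. In section 8, define ITT as all 93 randomised patients analysed in their allocated group. Use it for the primary FMA-UE comparison, with PP as a sensitivity analysis.
2. Replace LOCF with a likelihood-based repeated-measures model in which baseline FMA-UE is one of the outcomes (a constrained longitudinal model), or with multiple imputation. Either retains patients who have only a baseline score. Both assume data missing at random, so add a sensitivity analysis for data missing not at random.
3. In section 2.3, state that stopping treatment, withdrawal, an adverse event or a missing outcome does not remove a patient from the ITT set.
4. Reconcile the 4-week completion criterion in section 8 with the 12-week intervention in the Project summary, section 6, section 6.3 and Duration of the project, and with the 4 weeks in Study design.

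The cost is slightly more analysis work and the rewording of sections 8 and 2.3, plus the reconciliation of duration. The sample size does not change.

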**Study design**

This study will be a single-center, three-arm, parallel-group, assessors-blind randomized controlled trial. All the patients will be informed of the study content before the subject recruitment. The patients who meet the inclusion criteria and agree to participate in the study will sign the informed consent. As shown in the study flow chart (**Fig.1**), the patients will be randomly allocated into 3 groups with equal sample size: 1) CRT group; 2) CRT+RAT group; 3) CRT+ BWS-TCY group. The rehabilitation interventions will last 4 weeks. Patients’ upper-limb functions will be assessed using rating scales before and after the interventions.

[figure not shown]

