**3 Sample size**

We utilized G*Power software (v3.1.9.2, University Dusseldorf, Germany; available for download from http://www.psychologie.hhu.de) to determine the sample size for our study. The primary outcome evaluation index considered in this study was FMA-UE. Prior to commencing the formal experiment, 15 patients who met the inclusion criteria were divided into groups in a 1:1:1 ratio. Sample size calculation was conducted for the main objective, which focused on the treatment effect 4 weeks after surgery. The results of the preliminary experiment revealed the following mean ± standard deviation values after 4 weeks of intervention: TCY+CRT treatment (35.5±9.5), RAT+CRT treatment (34.28±9.58), and CRT alone (29.00±10.2). Based on the G*power two-factor repeated measures analysis of variance (ANOVA) F test, a total sample size of 84 cases was determined for a two-tailed test with a power of 80% and a significance level of 5% (alpha error). Considering a 1:1:1 allocation ratio and accounting for a 10% dropout rate, we estimated that a final total of 93 patients (31 in each group) would be required.

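### The primary analysis is an unadjusted repeated-measures ANOVA; adjusting FMA-UE for its pre-randomisation baseline would be at least as efficient at almost no cost, by an amount that depends on an unstated correlation

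*Protocol*

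**What the plan says.** Section 8 (Statistical method) states that "statistically significant differences in intra-group and inter-group data will be analyzed by repeated measurements of ANOVA". It names no covariate and does not say whether group, time or their interaction is the test of treatment. The same section says "The normality test of the measurement data is performed using the Shapiro-Wilk method" and then "Perform nonparametric statistical tests on data that do not conform to the normal distribution", without naming the nonparametric tests.

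Three other places bear on how to read this:

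- Section 3 (Sample size) states "The primary outcome evaluation index considered in this study was FMA-UE", and derives the total of 84 as "Based on the G*power two-factor repeated measures analysis of variance (ANOVA) F test".
- The Study design section states "Patients’ upper-limb functions will be assessed using rating scales before and after the interventions".
- Section 4 (Randomized grouping and allocation concealment) states "After baseline testing, each participant received an envelope containing a randomly assigned serial number to determine their group", so the baseline score cannot have been affected by treatment.

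**The concern.** A baseline measured before allocation can serve either as one more outcome level or as a covariate. A two-factor repeated-measures ANOVA on before-and-after scores, with no covariate named, uses it as an outcome level. The treatment test is then either the group-by-time interaction, which with two visits is the same as comparing change scores, or the group main effect, which averages in a visit that treatment could not have influenced. Adjusting for baseline is at least as precise as the first and far more precise than the second. What is at stake is precision on the primary comparison, from data the trial already collects.

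Two further features of section 8 raise a different kind of problem. If a normality check decides whether the parametric test is used, the primary hypothesis and effect measure are settled after the data are seen. Within-group significance is also weak evidence here. All arms receive active rehabilitation within six months of a first stroke, so improvement is expected in each, and a within-arm p-value compares no randomised groups.

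**Working it through.** **Inputs.** From section 3: pilot FMA-UE at 4 weeks of 35.5 (SD 9.5) for TCY+CRT, 34.28 (9.58) for RAT+CRT and 29.00 (10.2) for CRT; alpha 5%; 84 evaluable patients, 28 per arm. Assumed: equal mean baselines, equal variances at both visits, one baseline and one follow-up score, and r from 0.3 to 0.9.

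**Effect size.** Pooled SD = √[(9.5² + 9.58² + 10.2²)/3] = √95.36 = 9.77. The grand mean is 32.93 and the SD of the three means (divisor 3) is 2.82, so Cohen's f = 2.82/9.77 = 0.289 and f²N = 0.08345 × 84 = 7.01.

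**The plan's own figure.** The 84 cannot be uniquely reproduced, because section 3 states neither the number of measurements nor their correlation. The between-groups form, λ = f²Nm/[1+(m−1)ρ], gives 84 with m = 2 and ρ = 0.4, and also with m = 4 and ρ = 0.6; m = 2 with ρ = 0.5 gives 90. The interaction form used by G\*Power gives 33 with m = 2 and ρ = 0.5. A one-way ANOVA on follow-up scores alone needs 119. The sample size therefore does not settle which term is to be tested.

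**Comparison at N = 84** (three-arm F test, noncentral F, 2 numerator degrees of freedom):

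- Group-by-time, as change score: variance 2(1−r)SD², λ = 7.01/[2(1−r)], 81 denominator degrees of freedom.
- ANCOVA: variance (1−r²)SD², λ = 7.01/(1−r²), 80 denominator degrees of freedom.
- Group main effect, as the mean of the two visits: λ = 7.01 × 0.25/[(1+r)/2], 81 denominator degrees of freedom.

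The ratio of ANCOVA to change-score variance is (1−r²)/[2(1−r)] = (1+r)/2.

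| r | Variance ratio | Group-by-time: λ, power | ANCOVA: λ, power | Main effect: power |
|---|---|---|---|---|
| 0.3 | 0.65 | 5.01, 49% | 7.70, 68% | 28% |
| 0.5 | 0.75 | 7.01, 64% | 9.35, 77% | 25% |
| 0.7 | 0.85 | 11.68, 86% | 13.74, 91% | 22% |
| 0.8 | 0.90 | 17.52, 97% | 19.47, 98% | 21% |
| 0.9 | 0.95 | 35.05, about 100% | 36.89, about 100% | 20% |

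Simulations of the first two tests at r = 0.5 and 0.7 agreed with the formulas to within about 2 points. In sample-size terms, 80% power needs 119 patients by change score against 90 by ANCOVA at r = 0.5, 73 against 63 at r = 0.7, and 27 against 26 at r = 0.9.

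**Normality check.** If Shapiro-Wilk is applied at 5% to six cells (three arms, two visits), truly normal data fail at least once with probability about 1 − 0.95⁶ = 26%; simulation gave 24–28%. The power cost of switching is under 1 point if the fallback is Kruskal-Wallis on change. If the fallback uses follow-up scores alone, it is about 1 point at r = 0.5, 6 at 0.7 and 8 at 0.9. Type I error stayed at 4–5%.

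**BWS-TCY versus RAT.** The pilot difference is 35.5 − 34.28 = 1.22 points. Pairwise power with ANCOVA at unadjusted alpha 5% is 8–19% for r from 0.5 to 0.9.

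**The case against.** Group-by-time ANOVA is a valid comparison in a randomised trial, so choosing ANCOVA over it is a matter of efficiency, and the gain shrinks as baseline becomes more predictive: about 5 points at r = 0.7, 1 at 0.8 and nil at 0.9. An analysis plan that is not shown may name covariates and the tested term. All of this stands, and it limits the size of the point. It does not remove it, because the protocol itself commits to a named method, and adjustment is not materially worse at any r examined.

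Several stronger readings are tempting but are not supported:

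- **That the plan tests the group main effect, with power of only 20–28%.** No section names the tested term. Those figures show what follows if that term is read; they are not a description of the plan.
- **That within-group tests and the normality check waste power.** Within-group tests leave the power of the between-group test unchanged. The check costs little unless the fallback ignores baseline, which section 8 does not say.
- **That section 8 plainly replaces the primary ANOVA after the check.** It links Shapiro-Wilk to how data are summarised, gives a general sentence on nonparametric tests, and then adds the ANOVA. A switch is one reading, and the text should exclude it. Likewise, the intra-group wording may mean only the time factor.
- **That the software will discard patients with a missing visit.** Section 8 carries the last observation forward in the intention-to-treat analysis, so dropouts' later values are filled in. Whether that rule is sound is a separate question.
- **That baseline adjustment cures everything.** On its own it removes neither the within-group tests nor the switch, and at r = 0.3 or 0.5 it still falls short of 80% power.

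**Conclusion.** The point holds as a near-free gain in efficiency, with two accompanying faults of prespecification and interpretation. If baseline is a level of the time factor, which is a natural inference rather than stated text, baseline adjustment raises power over group-by-time by about 19 points at r = 0.3, 13 at 0.5, 5 at 0.7, 1 at 0.8 and nothing at 0.9. These figures rest on the 15-patient pilot means and SDs, equal baselines and variances, a single follow-up visit, and a correlation that the protocol does not give. The planned analysis is not invalid. Leaving the tested term unnamed matters as well, because the group main effect would be a poor test of treatment at every r examined.

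**What to change.** In section 8, make the primary analysis one prespecified between-group comparison of FMA-UE at the primary time point, adjusted for baseline FMA-UE by ANCOVA or by a mixed model of post-baseline visits, and report adjusted mean differences with 95% confidence intervals. The time point must be settled first: Study design, section 3 and section 8 refer to 4 weeks, while the Project summary and sections 6 and 6.3 refer to 12 weeks, and these passages must be reconciled. Report within-group change descriptively. Keep nonparametric or bootstrap results as sensitivity analyses, and state that no normality test changes the primary analysis.

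The cost is one residual degree of freedom and a matching edit to section 3, which now rests on the two-factor ANOVA and should state the assumed correlation. No extra patients, visits or measurements are needed. The change does not remedy the low power for BWS-TCY versus RAT.
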